#### ENDPOINTS

- First-and second-phase decay rates of plasma HIV-1 estimated by a biexponential viral-dynamics model
- Change in Plasma HIV RNA, CD4 cell count and proportion of patients with viral suppression at time points defined in the table below
- Percentage and number of CD3+CD8+CD38+HLADR+ (at time points defined in the table below)
- CCR5 and DR expression on CD4
- Plasma levels of IL-6, V-CAM
- Percentage and number of naïve and memory cells
- CD4 and CD8 response (SFC)
- Change from W00 to W48, and W96 in:
  - Fasting total cholesterol, LDL cholesterol, HDL cholesterol and triglycerides, apo-A1, apo-B, lipoprotein profiling.
  - Fasting glucose and insulin.
  - Coagulation Markers

#### SUB-STUDY COMPONENTS AND PROCEDURES

The assessments evaluate in the two different treatment strategies (see table 1, page 136).

- CD4 count at W00, day 2-3, W01, W02, W04, W08, W12, W18, W24, W32, W48, W64, W80, W96
- immunologic markers W00, W01, W02, W03, W04, W08, W12, W24, W48, W96:
  - level of expression of CCR5 on CD4+ T cells in association to immune activation as assessed by the quantification of CCR5 molecules on CD4 T cells in relationship with the level of CD38 expression on CD8 T cells and the proportions of activated HLA-DR+ CD4+ and CD8 T cells, and the proportions of naïve and memory CD4 T cells
  - numbers and functional competence of T cells against pathogens and HIV
- markers of endothelial activation and inflammation at W00, W02, W04, W08, W12, W24, W48, W96 (among those: Ultra-sensitive C-reactive protein, IL-6, V-CAM, serum amyloid A, serum amyloid P etc)
- coagulation markers: D-dimer, PAI-1, prothrombin fragment 1+2 at W00, W48, W96
- intensive lipids: total cholesterol, triglycerides, HDL-cholesterol; LDL-cholesterol, apo-A1, apo-B, lipoprotein profiling by NMR spectroscopy at W00, W04, W48, W96
- intensive glucose: fasting glucose and insulin, urine glucose (dipstick), fasting proinsulin, fasting C-peptide, HOMA at W00, W04, W48, W96
- plasma HIV-1 RNA at W0, day 2-3, W01, W02, W03, W04, W08, W12, W18, W24, W32, W48, W64, W80, W96
- total proviral DNA, episomal and integrated DNA, and spliced/unspliced RNA at W00, W01, W02, W03, W04, W08, W12, W24, W48, W96
- residual viral replication (HIV-1 RNA  $< 1$  copy/ml) at W24, W48, W96

Patients participating in this sub-study undergo additional blood sampling at W00, day 2-3, W01, W02, W03, W04, W08, W12, W24, W48, and W96 (see table 2, page 137). This

includes three extra visits to the study site (day 2-3, W01, W03) in addition to the core protocol visits.

This study requires core laboratories of immunology/virology with high tech performances in flow cytometry (these core laboratories could be in France, Italy, Germany, UK, Spain) and molecular virology, and local laboratories of immunology with very good performances in viable cell cryopreservation and reliable capacities of plasma storage.

Blood samples for analysis of immunologic and virologic markers need to be sent at room temperature and arrive at the closest core immunology lab during working hours and no later than 12h after sampling (see table 2, page 137).

In addition, this study requires expert laboratories to determine markers of endothelial activation and inflammation. These markers are measured on biobank samples of the core trial.

#### **Sample size:**

40 patients per arm

For viral dynamics, studies of optimal designs have shown that the scheduled measurements and number of subjects would be enough for 80% power for comparison of viral decays between treatment arms (Retout et al. Stat Med 2007; 26:5162-79). Assuming 10% of loss-to-follow-up and 25% of treatment interruption at W96, the inclusion of 80 patients allows for the evaluation of 60 patients still on treatment at the end of follow-up. This sample size (60) would be enough to show a difference of at least 0.5 log10 copies/ml in HIV RNA decline and a difference of at least 80 CD4+ cells/μL with a statistical power of 80%, assuming a common standard deviation of 0.67 log10 copies/ml and 102 cells/μL, respectively and using a Wilcoxon test.

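### Viral dynamics sub-study: 60 evaluable from 80 deducts only the 25% interruption; unless that figure already contains the 10% lost, 52 to 54 remain and power at W96 falls below 80%

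*Protocol*

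**What the plan says.** Appendix 15 of the protocol, under Sample size, plans "40 patients per arm". It makes two power statements.

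The first concerns viral decay. It claims 80% power from the measurement schedule and the number of subjects, citing work on optimal designs.

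The second concerns patients on treatment at W96. Its starting point is this: "Assuming 10% of loss-to-follow-up and 25% of treatment interruption at W96, the inclusion of 80 patients allows for the evaluation of 60 patients", meaning patients who remain on treatment when follow-up ends. The power claim is attached to that number: "This sample size (60) would be enough to show a difference of at least" 0.5 log10 copies/ml in HIV RNA decline and 80 CD4 cells/µL, at 80% power, with a Wilcoxon test and "a common standard deviation of 0.67 log 10 copies/ml and 102 cells/μL" respectively. The paragraph gives no significance level and does not say how the two attrition rates combine.

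Two sections of the main protocol bear on the meaning of those rates. Section 7.12 (Study regimen termination) keeps patients who stop their regimen in scheduled follow-up to the end of the trial. Section 7.16.3 (Loss to follow-up) describes those lost as patients who stop attending and whose status is unclear.

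**The concern.** The paragraph names two attrition assumptions, but the resulting number reflects only one. A patient counts as evaluable only if still on treatment at the end of follow-up, so has to escape both losses. The main protocol also treats stopping the regimen and being lost as different states. On that reading the evaluable number is too high, and the power quoted for it is too high as well.

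At stake is how a null comparison of HIV RNA decline or CD4 change at W96 would be read in this 80-patient sub-study. A reader would set it against 80% power when the planned numbers may support less. The primary endpoint, the core sample size of 800 and patient safety are not touched.

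**Working it through.** **Inputs (Appendix 15, Sample size).** 80 enrolled, 40 per arm; 10% lost to follow-up; 25% treatment interruption at W96; differences of 0.5 log10 copies/ml and 80 cells/µL; SDs of 0.67 and 102; Wilcoxon test; stated power 80%. Assumed here, because the paragraph is silent: two-sided α = 0.05, normally distributed data and equal arms.

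**Step 1: the plan's evaluable number.**
- 25% only: 80 × 0.75 = 60. This is the stated figure, exactly.
- 10% only: 80 × 0.90 = 72.
- Both, successively: 80 × 0.90 × 0.75 = 54.
- Both, additively: 80 × (1 − 0.10 − 0.25) = 80 × 0.65 = 52.

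So 60 follows only if the 10% is left out or is already inside the 25%. The other two results are 6/60 = 10% and 8/60 = 13% smaller.

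**Step 2: the plan's power at 60.** Standardised differences are 0.5/0.67 = 0.746 (RNA) and 80/102 = 0.784 (CD4). For the Wilcoxon test under normality, multiply the number per arm by 3/π = 0.955. The normal approximation is then

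power = Φ( d × √(0.955 n / 2) − 1.96 ).

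With n = 30 per arm: RNA Φ(0.746 × 3.785 − 1.96) = Φ(0.86) = 80.6%; CD4 Φ(0.784 × 3.785 − 1.96) = Φ(1.01) = 84.3%. The noncentral t version gives 79.3% and 83.1%, and a simulation of the rank-sum test (40,000 runs) gives 79.4% and 83.0%. The stated 80% at 60 therefore reproduces for RNA and is exceeded for CD4.

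**Step 3: power with both losses deducted.**

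| Evaluable (per arm) | RNA: noncentral t | RNA: normal approx. | RNA: simulation | CD4: noncentral t | CD4: normal approx. | CD4: simulation |
|---|---|---|---|---|---|---|
| 60 (30) | 79.3% | 80.6% | 79.4% | 83.1% | 84.3% | 83.0% |
| 54 (27) | 74.8% | 76.4% | 74.8% | 78.9% | 80.4% | 79.0% |
| 52 (26) | 73.1% | 74.8% | 73.0% | 77.3% | 78.9% | 76.8% |

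**Step 4: difference detectable with 80% power** (noncentral t, same Wilcoxon factor).

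| Evaluable | HIV RNA (log10 copies/ml) | CD4 (cells/µL) |
|---|---|---|
| 60 | 0.505 | 76.8 |
| 54 | 0.533 | 81.2 |
| 52 | 0.544 | 82.8 |

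RNA has no reserve at 60, so any further loss takes it below 80%. CD4 starts about three points above 80% and ends one to three points below.

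**The case against.** The best defence is that the 25% is the all-cause share off treatment at W96, with the 10% lost inside it. The evaluable set is patients still on treatment, and someone lost to follow-up is not in that set. Section 7.12 can even explain why both rates are given: because patients who stop treatment stay in follow-up, a 10% loss leaves 72 followed, of whom 60 are still on treatment. Section 2.2.1 reports treatment discontinuation by W96 of 17% and 23% in the two arms of the cited first-line trial of boosted darunavir against boosted lopinavir. A total of 25% is close to those figures. Separate losses imply 26/80 = 32.5% or 28/80 = 35% off treatment or lost, well above both.

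This defence stands as a possibility. The text does not exclude it, and under it 60 is correct and about 80% power holds. It does not remove the point. The paragraph presents the two rates as parallel assumptions, nowhere says that one contains the other, and on the nested reading the 10% plays no part in reaching 60.

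Three stronger inferences are tempting, and the documents do not support them:
- **That 60 is simply an error and 80% power is definitely not delivered.** This would require the 25% to exclude those lost, which the protocol does not settle.
- **That the sub-study's power fails as a whole.** The viral decay statement rests on the measurement schedule and the number of subjects, not on 60.
- **That the shortfall holds at every visit and equally for both outcomes.** The attrition is tied to W96 and the end of follow-up. Nothing is stated for earlier visits, and CD4 is affected much less than RNA.

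**Conclusion.** The stated 60 does not follow from both stated losses unless one is contained in the other, and the paragraph does not say that it is. If the losses are separate, 52–54 patients are evaluable on treatment at W96. Power is then about 73–75% for the RNA difference, some 5–7 points below the stated 80%, and about 77–79% for CD4. With the normal approximation, CD4 at 54 still reaches 80.4%, so that shortfall is marginal.

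These figures rest on a two-sided 5% level, normal data and equal arms, none of which the paragraph states. The sentence that 60 would suffice is sound in itself; the step from 80 to 60 is what is open. The matter is confined to the W96 on-treatment comparisons in one sub-study, but it deserves correction because a number and the power built on it cannot be derived from the text as written.

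**What to change.** First establish from the sub-study's planning records whether the 25% includes the 10%.

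- **If it does:** add a clause saying that 25% is the all-cause proportion off treatment or lost by W96, and keep 60 and the power statement.
- **If it does not:** restate the evaluable number as 52–54. Then either give power as about 73–75% (RNA) and 77–79% (CD4), or give the differences detectable with 80% power as about 0.53–0.54 log10 copies/ml and 81–83 cells/µL.

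In both cases, state the significance level and sidedness. Leave the viral decay sentence as it is.

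The cost is one paragraph in Appendix 15 and, in the second case, a slightly less favourable power statement. Section 9.1 records that trial enrolment was complete by amendment 5.0, and no further enrolment is needed.

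### Viral dynamics sub-study (Appendix 15): 60 evaluable patients applies only one of the two stated losses; both leave 52–54, with HIV RNA power about 73–74% instead of 80%

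*Protocol*

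**What the plan says.** Protocol Appendix 15, under the sample size heading, sets the sub-study at "40 patients per arm". It makes two statements about power.

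- The comparison of viral decays between arms is said to have 80% power, on the basis of cited work on optimal designs, the measurement schedule and the number of subjects.
- The end-of-follow-up comparison has its own calculation. It starts from two rates, "Assuming 10% of loss-to-follow-up and 25% of treatment interruption at W96", and concludes that "the inclusion of 80 patients allows for the evaluation of 60 patients still on treatment at the end of follow-up". It goes on: "This sample size (60) would be enough to show a difference of at least 0.5 log" in HIV RNA decline, and "a difference of at least 80 CD4" cells/μL, with 80% power by a Wilcoxon test. The standard deviations are given by "assuming a common standard deviation of 0.67 log" and "copies/ml and 102 cells/μL, respectively".

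No significance level is given for this calculation. The paragraph does not say that either loss rate includes the other.

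**The concern.** Two attrition rates are stated, but the evaluable number matches only one of them. The next sentence then takes that number as the basis for 80% power. The design sits close to 80% at 60 patients, so there is little slack to absorb six to eight fewer. If the figures stay as they are, a null W96 result for HIV RNA would be read as coming from an 80%-powered comparison when, on the sub-study's own assumptions, the power was lower.

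**Working it through.** **Inputs (Appendix 15, sample size).** 80 patients, 40 per arm; losses of 10% and 25% at W96; HIV RNA difference 0.5 log10, SD 0.67; CD4 difference 80 cells/μL, SD 102; Wilcoxon test; target power 80%. *Assumption:* two-sided alpha 0.05, since none is stated.

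**1. The plan's evaluable number.**
- 25% alone: 80 × (1 − 0.25) = 60. This reproduces the plan.
- Both rates in turn: 80 × (1 − 0.10) × (1 − 0.25) = 54, or 27 per arm.
- Both rates added: 80 × (1 − 0.10 − 0.25) = 52, or 26 per arm.

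**2. The plan's step from 60 patients to 80% power.** Standardised differences are 0.5/0.67 = 0.746 and 80/102 = 0.784. The normal approximation with the Wilcoxon efficiency factor 3/π = 0.955 is

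power = Φ(d × √(n × 0.955 / 2) − 1.96), with n per arm.

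At n = 30, HIV RNA: 0.746 × √14.32 − 1.96 = 0.864, so power is 80.6%. CD4: 0.784 × √14.32 − 1.96 = 1.008, so power is 84.3%. The step from 60 to 80% therefore holds, which also supports the alpha assumed here. The fault lies only in the 60.

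**3. Power at the corrected numbers.** The simulation used normal data and a two-sided Wilcoxon test.

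| Per arm | HIV RNA, simulation | HIV RNA, formula | CD4, simulation | CD4, formula |
|---|---|---|---|---|
| 30 | 79% | 80.6% | 82% | 84.3% |
| 27 | 74% | 76.4% | 78–79% | 80.4% |
| 26 | 73% | 74.8% | 76–77% | 78.9% |

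For HIV RNA every method tried falls below 80% at 26–27 per arm. Even the normal approximation without the Wilcoxon penalty gives 78.3% and 76.8%. Noether's formula gives 72.6% and 71.0%. For CD4 the shortfall is one to four points by simulation, and the formula just reaches 80% at 27 per arm.

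**4. Differences detectable with 80% power.** By simulation, 80% power needs about 31 per arm for HIV RNA and 28 for CD4. Scaling by the square root of n:
- HIV RNA: 0.5 × √(31/27) = 0.54 and 0.5 × √(31/26) = 0.55 log10.
- CD4: 80 × √(28/27) = 81.5 and 80 × √(28/26) = 83.0 cells. Solving by simulation gives 81.7 and 83.3, so about 82–83.

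**5. Enrolment that would keep 60.** 60/(0.90 × 0.75) = 88.9 and 60/0.65 = 92.3, or 90 to 94 patients with equal arms.

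**The case against.** The best defence is that 60 is exact if the 10% lost are counted inside the 25%. The quantity wanted is patients still on treatment, and someone lost to follow-up is not observed on treatment. This reading is possible, and one clause would settle it. It is the weaker reading, for two reasons. It leaves the 10% with no role in the calculation. It also blurs categories that the protocol keeps apart: sections 5.1 and 7.12 keep patients who change or stop the regimen in follow-up, and section 7.16.3 defines loss to follow-up separately.

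It is also fair to say that the effect is small. At the plan's own 60, simulated HIV RNA power is already 79%, so the attrition slip costs about five to six points. For CD4 the shortfall depends partly on the method. Both points stand, and they limit the size of the finding.

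A reader might infer more than the text supports:

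- *That the sub-study will compare only patients still on treatment and so give up randomisation.* The paragraph sizes the study; it fixes no analysis set. Section 2.7.2 describes these appendices as summaries, section 9.4 leaves analysis detail to a separate plan, and section 11 keeps patients given other treatment in the analysis by allocated option.
- *That all of the sub-study's power fails.* The statement on viral decay rates does not use the 60.

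**Conclusion.** Wrong as written. The two stated rates leave 52–54 evaluable on-treatment patients, not 60. Wilcoxon power for 0.5 log10 HIV RNA is then about 73–74%, clearly short of the stated 80%. For 80 CD4 cells it is about 76–79%, marginally short. These figures assume two-sided alpha 0.05, normally distributed data, equal attrition in the two arms, and that the 10% and 25% are separate losses. If the 25% already contains the 10%, the 60 stands and the fault is one of wording. The finding is confined to the W96 calculation of an 80-patient sub-study. It does not touch the viral decay power statement, the main trial's primary analysis or its 800-patient sample size.

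**What to change.** Amend the sample size paragraph of Appendix 15 in one of these ways:

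- restate the evaluable number as 52–54, with power of about 73–74% (HIV RNA) and 76–79% (CD4);
- restate the differences detectable with 80% power as about 0.54–0.55 log10 copies/ml and 82–83 cells/μL; or
- if it was the intention, say that the 25% includes losses to follow-up, and keep 60.

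In each case state the alpha used. The cost is one or two sentences. Section 9.1 records that enrolment is complete, so correcting the figures is the practical course rather than adding patients. No change of analysis population is needed.

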#### **Coparticipation**

Patients participating in this sub-study should be encouraged to participate also in the bone substudy or the neurocognitive function sub-study.

Table 1: Viral and immunologic dynamics and inflammation sub-study: Overview of planned assessments

| Visit                                                             | W -6 | W 00 | Day 2-3 | W 01 | W 02 | W 03 | W 04 | W 08 | W 12 | W 18 | W 24 | W 32 | W 48 | W 64 | W 80 | W 96 |
|-------------------------------------------------------------------|------|------|---------|------|------|------|------|------|------|------|------|------|------|------|------|------|
| Study procedures                                           |      |      |         |      |      |      |      |      |      |      |      |      |      |      |      |      |
| Informed consent                                                  | X    | (X)  |         |      |      |      |      |      |      |      |      |      |      |      |      |      |
| Local lab assessments                                      |      |      |         |      |      |      |      |      |      |      |      |      |      |      |      |      |
| Plasma HIV-1 RNA                                      |      | (X)  | X       | X    | X    | X    | (X)  | (X)  | (X)  | (X)  | (X)  | (X)  | (X)  | (X)  | (X)  | (X)  |
| CD4 cell count                                        |      | (X)  | X       | X    | X    |      | (X)  | (X)  | (X)  | (X)  | (X)  | (X)  | (X)  | (X)  | (X)  | (X)  |
| Planned centralised assessments                            |      |      |         |      |      |      |      |      |      |      |      |      |      |      |      |      |
| Residual viral replication                                        |      |      |         |      |      |      |      |      |      |      | X    |      | X    |      |      | X    |
| Proviral DNA, episomal and integrated DNA, spliced/ unspliced RNA |      | X    |         | X    | X    | X    | X    | X    | X    |      | X    |      | X    |      |      | X    |
| PBMC activation                                                   |      | X    |         |      | X    |      | X    | X    | X    |      | X    |      |      |      |      | X    |
| Immunologic markers (PBMC and serum)                              |      | X    |         | X    | X    | X    | X    | X    | X    |      | X    |      | X    |      |      | X    |
| Endothelial activation and inflammation                           |      | X    |         |      | X    |      | X    | X    | X    |      | X    |      | X    |      |      | X    |
| Intensive lipids                                                  |      | X    |         |      |      |      | X    |      |      |      |      |      | X    |      |      | X    |
| Intensive glucose                                                 |      | X    |         |      |      |      | X    |      |      |      |      |      | X    |      |      | X    |
| Coagulation Markers                                               |      | X    |         |      |      |      |      |      |      |      |      |      | X    |      |      | X    |

1 Assessments in parentheses (X) are performed in the core trial and do not need to be programmed specifically for the sub-study.

Table 2: Viral and immunologic dynamics and inflammation sub-study: Specific laboratory assessments in addition to core protocol sampling, sampling volumes and sample circuit

| Visit                                                               | W00             | Day 2-3 | W01             | W02             | W03             | W04             | W08             | W12             | W18 | W24             | W32 | W48             | W64 | W80 | W96             |
|---------------------------------------------------------------------|-----------------|---------|-----------------|-----------------|-----------------|-----------------|-----------------|-----------------|-----|-----------------|-----|-----------------|-----|-----|-----------------|
| Local lab                                                           |                 |         |                 |                 |                 |                 |                 |                 |     |                 |     |                 |     |     |                 |
| Plasma HIV-1 RNA                                                    |                 | X       | X               | X               | X               |                 |                 |                 |     |                 |     |                 |     |     |                 |
| CD4 cell count                                                      |                 | X       | X               | X               |                 |                 |                 |                 |     |                 |     |                 |     |     |                 |
| Sampling for immediate shipment to core immunology lab  | X               |         | X               | X               | X               | X               | X               | X               |     | X               |     | X               |     |     | X               |
| Total amount blood sample (ACD or heparin tubes) for centralisation | 50 mL           |         | 5 mL            | 5 mL            | 5 mL            | 30 mL           | 30 mL           | 30 mL           |     | 50 mL           |     | 50 mL           |     |     | 50 mL           |
| Temperature of shipment                                             | RT  |         | RT  | RT  | RT  | RT  | RT  | RT  |     | RT  |     | RT  |     |     | RT  |

1 Samples must arrive at the core immunology laboratory during working hours and no later than 12h after sampling.

2 RT = room temperature

